**Table 1 Tab1:** **Design of the study, time schedule**

**Outcomes**	**Month:**	**1**	**2**	**3**	**4**	**5**	**6**	**7**	**8**	**9**	**10**	**11**
		T0	I, T1			T2, F1			F2			T3
**Nursing staff**	**Primary**											
	Emotional Burnout: (UBOS)	X	X			X						X
	**Secondary**											
	Emotional workload (NPI-NH)	X				X						X
	Work satisfaction (LAKS)	X				X						X
	Emotional reactions during work (subscale VBBA)	X				X						X
	Knowledge	X	X									X
**Residents**	**Secondary**											
	Challenging behavior (NPI-NH)	X				X						X
	Agitation (CMAI)	X				X						X
	Quality of life: (Qualidem)	X				X						X
	Social Engagement (RISE)	X				X						X
	Perceived Quality of care (Self-developed)	X				X						X
Additional measurements												
	Approaches towards dementia (ADQ)	X				X						X
	Organizational culture (CVF)	X				X						X

I = Intervention (training program).

T = Time of measurement.

F = Follow up session of training program.

UBOS = Utrecht Burnout Scale.

NPI-NH = Neuro Psychiatric Inventory Nursing Home.

CMAI = Cohen Mansfield Agitation Index.

Qualidem = Quality of life of residents with dementia in nursing homes.

RISE = Revised Index for Social Engagement for long-term care.

ADQ = Approaches towards Dementia Questionaire.

CVF = Competing Values Framework of organizational culture.

VBBA = Vragenlijst Beleving en Beoordeling van de Arbeid.

**Figure 1 Fig1:**
[figure not shown]
**Design of the TENSE-study.**

### Inclusion criteria

Nursing homes will be included if:they have at least two DSC Units;nursing staff members, psychologist and physician work on one of these units exclusively;one care team cares for at least fifteen residents that are diagnosed with dementia;participating units have not planned a reorganization or other interventions that can influence the study within half a year before or during the study.

Inclusion criteria for residents are:dementia according to DSM-IV-TR criteria [43],living in the nursing home for more than one month.

Inclusion criteria for the nursing staff are:being employed for at least three months and not expected to be transferred to another unit within the study period,working more than one day a week.

### The intervention

The educational program has three core elements for increasing its usefulness:an individually tailored make up based on interviewing staff, management and nursing staff about their wishes and needs;two follow up sessions, to enable continuous education;supervision, monitoring, facilitation and stimulation by the psychologist, middle management and other staff on the use of the newly learned techniques.

It has the following content:providing knowledge about dementia,educating about the origins of challenging behavior and how to manage it,educating how to recognize distress caused by challenging behavior in yourself and in colleagues,practicing how to gather information on resident and environmental factors that cause challengingbehavior,practicing how to signal signs of impending challenging behavior,practicing general behavior management skills that can be used in approaching the resident,practicing how to use a standardized method to manage challenging behavior, which is integrated in the multidisciplinary work processes and forms that are used in the nursing home.

The content of the educational program is based on three conceptual models regarding challenging behavior: (1) The Progressively Lowered Stress Threshold Theory (PLST) [44], (2) the Unmet Needs [45] model and (3) the ABC model [46-48]. These three theories are used to explain possible antecedents for different forms of challenging behavior. The PLST (1) states that residents with dementia are less able to cope with stress as they get tired during the day. Unmet Needs theory (2) claims that challenging behavior is caused by the decreased capability of clients with dementia to explain their needs. The ABC model (3) is used for analyzing the antecedents and consequences of behavior. It is developed by Cohn et al. [22], and introduced in the Netherlands by Hamer en Voesten [46,47]. The ABC model is based on learning theory [49] and states that behavior (B) is triggered by internal and external stimuli, (Antecedents (A)) that bring the resident to this behavior. Behavior is reinforced by Consequences (C). In this program the ‘D’ is added to the ABC model, regarding thoughts and feelings of nursing staff about the challenging behavior. (in Dutch this is the “D” from “Denken” which means: “think”). The ABCD model is used for describing challenging behavior. Participants gather extensive information about antecedents in the past (personality, important life events and coping style), the present (cognitive- and communication capacities), the environment (the unit, other residents and the nursing staff) and the family (interaction with the resident).

A pilot program/training was run with one group of fifteen nurses. This training course was judged as very good by the participants and led to a few minor adjustments of the program (using more case studies brought in by the participants). The training program was performed by one trainer.

### The process of implementation

Before the 3-day course starts an extensive semi structured interview is conducted by the trainer with the psychologist, the elderly care physician (ECP) [50], the team manager and some members of the nursing staff to explore current (multidisciplinary) work processes and collect wishes and needs of the institution for tailoring the program. In this interview the following topics are discussed (1) in what way does the actual way of working differ from an ideal situation? (2) the context for change; is the nursing staff motivated to change?, (3) in what way does the organization supply help to facilitate changes in work processes. (4) what barriers and facilitators for the process of change exist in the nursing home. After the interview a plan is presented to the care-organization which describes in what way the intervention is tailored to the care-organization by training the elements that need to be changed [51]. The researcher receives the forms used by nursing staff on the unit for observing and analyzing behavior and for making a behavioral management plan, and incorporates these forms into the educational program. This way, nursing staff will not be confronted with new forms which differ from the ones they use in daily practice. The training program was provided by a very experienced professional trainer of nursing staff.

#### The course

The 3-day course is offered to the complete unit-team and consists of three lessons of 2.5 hours, provided once per week or, once every two weeks. During the course, several team members are made responsible for various tasks, such as observing the resident’s behavior; observing stress caused by the challenging behavior; making an action plan; controlling the use of the plan; and involving the physician and/or psychologist at the right moment. Furthermore, the unit managers also receive the training so they can facilitate and reward the use of the newly learned techniques. Two follow up sessions are carried out. These are designed to stimulate the process of managing challenging behavior methodologically and are tailored to the situation in the organization.

#### First session: causes of challenging behavior and consequences for the resident. Introducing the ABCD model to analyze challenging behavior

Knowledge about dementia and causes for challenging behavior are explained. Several theories explaining challenging behavior are used, including the Unmet Needs theory and the Progressive Lowered stress Threshold Theory (PLST). Using the ABCD model participants also analyze their own role in causing and (accidentally) rewarding challenging behavior. They receive a form with which they can describe a resident that exhibits challenging behavior. These cases are used in the second session.

#### Second session: consequences of challenging behavior for nursing staff

Participants bring in two or more cases from their unit. These are used to analyze challenging behavior. The information they have gathered is used to answer the next five questions; (A) what unmet need is the resident expressing with this challenging behavior? (B) How does the resident cope with (a lower) stress (threshold) now and difficulties given his cognitive and verbal capacities. (C) What is the influence of the environment on the clients behavior? (D) What is the influence of the nursing staff on the challenging behavior? (E) What is the influence of the family of the resident on the challenging behavior? In doing this, it becomes clear for nursing staff on which part they need more information.

#### Third session: a plan of action

Before the third session nursing staff gathers the information they need and also read a paper about making a plan of action [52]. The third session concerns making the action plan. Nursing staff learn to use the sequence of “problem – goal – action” to decide what action has to be taken. Nursing staff decides which aspects of the training they want to practice in the next three months.

Subsequently, the trainer writes a report about the training that consists of the way participants want to manage the challenging behavior after the training and the wishes for future training and sends it to the psychologist of the nursing home. The psychologist, the unit manager and the elderly care physician can use it to support the nursing staff in managing challenging behavior and incorporate what they have learned in daily practice.

#### Follow-up sessions

There is a follow up session at three and six months after the 3-day course. These follow up sessions are tailored to the situation in the nursing home after interviewing the unit manager, the psychologist and the nursing staff about the implementation of the acquired knowledge in the training course, their experiences and the subsequent training they still need. If possible the trainer joins in a regular team meeting. Follow up sessions are all designed to stimulate the process of managing challenging behavior methodologically but can train different aspects in each nursing home.

Tailoring the training course to suit it to the unit is done by applying two follow up meetings in which parts of the training program that need additional attention are addressed [53]. Furthermore, qualitative information on current multidisciplinary care processes and the level of knowledge of nursing staff on the individual units is collected before the start of the training program. This information is used to determine how the program and the newly acquired knowledge can be integrated in the unit’s multidisciplinary care process, and to determine whether the program’s content must be preceded by additional information to increase the participants’ initial level of knowledge.

### Outcome measures

Nursing staff fills in questionnaires with questions about themselves and the residents at four points in time on the outcome measures described below. To prevent information bias, nursing staff are not informed about the scores [54]. Data is collected using a secured web based questionnaire (www.tense-studie.nl).

#### Primary outcome measure

Stress is operationalized using the Dutch version of the Maslach Burnout Inventory (Maslach and Jackson, [55]), the ‘Utrecht Burnout Scale – C’ (Schaufeli and van Dierendonck, [56]). This scale measures three components of burnout: emotional exhaustion, depersonalization and decreased personal accomplishment. Higher scores on this six-point scale suggest higher stress [57]. Internal consistency is good with Cronbach’s alpha of .70 and over [57], and the validity of the three factor structure has been confirmed [57].

#### Secondary outcome measures

##### Nursing staff

To measure emotional workload, the subscale ‘emotional workload’ of the Neuro Psychiatric Inventory Nursing Home version is used (for a description of the NPI NH: see below).

*Work satisfaction* is measured with the Dutch “Leiden Quality of work Questionnaire”. The Leiden Quality of Work Questionnaire scale consists of seven subscales: completeness of the job, organizational tasks, cycle length, complexity, autonomy, possibilities for social contact, and feedback. These seven scales have a satisfactory internal reliability [58].

*Stress reactions* at work are assessed with the subscale” emotional reactions at work” from the: “Vragenlijst Beleving en Beoordeling van de Arbeid” (VBBA). This four-point scale can be considered as uni-dimensional, and reliability and validity are good [59].

A *knowledge-test* based on knowledge tests found in literature [60-70] is used before and after the educational program, and at the final measurement, this test was run in a pilot with 25 nurses in a nursing home.

##### Residents

*Challenging behavior* is assessed using the Neuro Psychiatric Inventory-Nursing home (NPI-NH) and the Cohen-Mansfield Agitation Inventory (CMAI). The NPI-NH: a comprehensive assessment scale including the following symptoms: delusions, hallucinations, agitation, depression, anxiety, euphoria, apathy, disinhibition, irritability, aberrant motor behavior, night-time disturbances and eating change. The frequency (F) is rated on a four-point (1–4) Likert scale and the severity (S) is rated on a three-point (1–3) Likert scale, yielding an F X S score. When a symptom is not present, the F and S scores are both zero. The F X S score thus contains information about prevalence, frequency, and severity (range 0–12 for each symptom). A Dutch translation of the NPI has also shown to be reliable and valid [49].

The Cohen-Mansfield Agitation Inventory (CMAI) consists of 29 items about agitation and aggression and has been validated for use in care homes in the Netherlands [71]. The CMAI measures the frequency (on a seven point scale from never to several times an hour) of agitation during the preceding two weeks (total score range: 29–203). The NPI-NH and the CMAI are commonly used in the nursing home so nursing staff is used to these forms.

For measuring *Quality of life* the Qualidem is used. The Qualidem includes 37 items and is a multidimensional scale specifically designed for institutionalized residents with dementia. The Qualidem is designed by Ettema et al. [72,73] and evaluated by Bouman [74]. It measures the quality of life for people with dementia living in residential care settings. It assesses quality of life of all residents even those with severe dementia [74]. It consists of nine subscales: care relationship, positive affect, negative affect, restless tense behavior, positive self image, social relation, social isolation, feeling at home and having something to do.

Social engagement will be measured by the Revised Index for Social Engagement (RISE) developed by Gerritsen et al. [75] and based on the Index for Social Engagement (Mor et al., [76]). This scale describes social engagement for residents living in long-term care. Reported internal consistency and interrater and intrarater reliability are sufficient [75].

#### Additional measurements

As it has been shown that attitudes of nursing staff about dementia and on the other hand organizational culture may influence the extent to which innovations are executed or may influence the strength of the intervention effect, possible influencing factors and their association with the primary and secondary outcomes will be investigated. To this aim the following scales are included in the study:

##### Approaches about people with dementia

To measure nursing staff attitudes, the Approaches towards Dementia Questionnaire (ADQ: Lintern & Woods, [77]) is assessed. This scale consists of 19 statements about people with dementia measured on a five point Likert scale. This scale has two subscales, one indicates the staff member’s degree of hopefulness and the other indicates the extent to which a person-centered approach is exposed. The subscales have shown good reliability and have been validated against direct observation of the quality of staff care interactions [78].

##### Organizational culture

Organizational culture will be measured with the Competing Values Framework of organizational culture (CVF) for long-term care as developed by Scott-Cawiezell et al. [79]. The CVF assesses the 6 dimensions of the competing values framework in 6 items. These are: dominant organizational characteristic, administration, management style, organizational glue, strategic emphasis and criteria for success [80].

### Process evaluation

Along with the intervention study a process evaluation is carried out according to the model of Leontjevas et al. [81]. It is important to study whether the educational program was delivered as intended to draw accurate conclusions on its effects (Hulscher et al., [51]). Also, process evaluation enables improvement of the intervention, enables others to replicate the program, facilitates future comparison between studies (Hulscher et al., [51]) and enables the transition from research evidence into health practice (Grol and Grimshaw, [82]).

To study the reach of and compliance to the program, attendance to sessions of the nursing staff is registered. Dropout of residents by death or relocation and replacement of them are registered. To register the feasibility and relevance of the training program nursing staff is asked to evaluate the training. Barriers and facilitators for the implementation of the changes nursing staff is willing to do are gathered. At the end of the study ECP’s, unit managers and psychologists will be asked in a semi-structured interview if they have perceived changes in the management of challenging behavior on the unit.

### Sample size

For calculating the appropriate sample size we use the following assumptions:

DSCU consist of 20 residents on average [49], with 18 nursing staff on average eligible for inclusion.

For the primary outcome, stress experienced by nursing staff, we assume that our intervention leads to a 4 point decrease on the subscale Emotional Exhaustion of the Maslach Burnout Inventory based on the reduction found by Yun-Hee Jeon et al. [83] who found a reduction of 2.5 points after three months and 4.4 points after nine months in her study in which she used training and support to evaluate person centred care to dementia care mapping and usual care. Based on these assumptions and based on a significance level alpha of 0.05, a power of 0.80 and a conservative estimated correlation between two measurements of .6 [84] and an ICC of 0.05 we need a sample size of 121 nursing staff members and 121 residents in each group for ANCOVA analysis based on equal sample sizes which implies including 16 clusters; eight intervention and eight control units. In order to account for intra cluster correlations, Multi Level Analysis will be used. Nursing staff that moves to another job will be replaced, the nursing staff replacing them will join in the course. To compensate for nursing staff not replaced in time we will add an extra unit so we use nine intervention and nine control units this results in 135 nursing staff members and 135 residents in the intervention group and an equal amount in the control group.

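### The 16-cluster figure does not follow from the listed 18 staff per unit and, on a cluster-level t test, falls short of 0.80 power, so part or all of the ninth unit restores power instead of covering turnover

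*Protocol article*

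**What the plan says.** The Sample size section of the protocol article introduces its inputs with "For calculating the appropriate sample size we use the following assumptions". They are units of 20 residents on average, "with 18 nursing staff on average eligible for inclusion", "a 4 point decrease on the subscale Emotional Exhaustion of the Maslach Burnout Inventory", an alpha of 0.05, "a power of 0.80 and a conservative estimated correlation between two measurements of .6", and an ICC of 0.05. From these it obtains 121 staff and 121 residents per group for an ANCOVA, "which implies including 16 clusters; eight intervention and eight control units".

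It then says that multilevel analysis will be used and that leavers will be replaced. It adds one unit per arm for a single stated purpose: "To compensate for nursing staff not replaced in time we will add an extra unit". That gives nine units and 135 staff per arm. The Discussion repeats that the sample size allows for staff who change jobs.

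The section gives no SD, no cluster size for the design effect, no participation rate, no turnover rate and no reference distribution for the test.

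**The concern.** Two steps do not connect.

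First, the number of units is presented as a consequence of the listed inputs, but 18 staff per unit does not lead from 121 to eight units. A different unit size, about 15, was used and is not explained. Unit size enters twice, in the design effect and in the division that gives the number of units, so the choice changes the result.

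Second, the number of individuals is calculated first and the number of clusters is then obtained by division. That order suggests a normal-theory formula, because cluster-level degrees of freedom depend on the number of clusters. With eight or nine units per arm, the difference between a normal and a t reference is not negligible. The usual remedy is roughly one more cluster per arm. The plan adds exactly that, but assigns it wholly to staff turnover.

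At stake is how a null result on the primary outcome would be read: against a claimed 0.80 power plus a reserve for turnover, neither of which the article demonstrates.

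**Working it through.** **Inputs from the Sample size section:** difference 4 points; alpha 0.05 (two-sided assumed, as sidedness is not stated); power 0.80; correlation 0.6, so the ANCOVA factor is 1 − 0.36 = 0.64; ICC 0.05; 121 per arm in 8 units; 135 per arm in 9 units. **Not given:** the SD and the cluster size m in the design effect. I take m = 15 (implied by the totals), 18 (listed for staff) and 20 (listed for residents) as assumptions.

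**1. Unit count.** 121/18 = 6.7, so seven units per arm. Eight units of 18 would be 144 and nine would be 162. The article's totals give 121/8 = 15.1 and 135/9 = 15.0 per unit; 15/18 = 83%. Residents show the same gap: 20 per unit listed, 15 used.

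**2. The figure of 121.** The usual formula is n per arm = 2 × (1.960 + 0.842)² × (SD/4)² × 0.64 × [1 + (m − 1) × 0.05], with (1.960 + 0.842)² = 7.849. Without an SD, 121 cannot be reproduced independently; I can only solve for the SD that yields it.

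- m = 15: design effect 1.70; (SD/4)² = 121/(2 × 7.849 × 0.64 × 1.70) = 7.085; SD = 10.65
- m = 18: design effect 1.85; SD = 10.2
- m = 20: design effect 1.95; SD = 9.9

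**3. Power with cluster-level degrees of freedom.** Effective n per arm is (units × staff per unit)/design effect. It was 121/1.70 = 71.2, 121/1.85 = 65.4 or 121/1.95 = 62.1 in the assumed derivation. The non-centrality is 2.802 × √(effective n achieved / effective n in the derivation), referred to a non-central t with 2k − 2 df for k units per arm. The SD cancels, so these results do not depend on its value.

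Effective n achieved per arm:

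- 8 × 15 = 120: 120/1.70 = 70.6, 14 df
- 9 × 15 = 135: 135/1.70 = 79.4, 16 df
- 9 × 13.44 = 121: 121/1.622 = 74.6, 16 df. This is the loss that the ninth unit could absorb in head count, 1 − 121/135 = 10.4%; it is not a stated turnover rate.

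| Design effect behind 121 used | 8 × 15, 14 df | 9 × 15, no loss, 16 df | 9 × 13.44, about 10% loss, 16 df |
|---|---|---|---|
| m = 15 | 0.74 | 0.79 | 0.77 |
| m = 18 | 0.77 | 0.83 | 0.80 |
| m = 20 | 0.79 | 0.84 | 0.82 |

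Worked example, m = 15 and 8 × 15: non-centrality 2.802 × √(70.6/71.2) = 2.79. Power is 0.797 on the normal reference and 0.737 on t with 14 df.

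**4. Sensitivity.** For m = 15, 20% loss (9 × 12) gives 0.74. If alpha is one-sided and m is about 15, power is 0.76 with 16 clusters and 0.81 with 18. If the degrees of freedom are counted by the within-organization pairs (7 and 8), and pairing is credited with no reduction in variance, power is 0.67 and 0.74.

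**The case against.** The best reply is that the article never says how 121 was obtained. A t-based or few-cluster-corrected calculation is not excluded; for instance, 121/18 rounds up to seven, and one more unit makes eight. A condensed article may leave the formula and SD to the full protocol, and the degrees-of-freedom method of the mixed model to the analysis plan. This stands to the extent that the power shortfall is conditional on a normal formula. It does not remove the gap in the unit count, which the article itself presents as following from its assumptions.

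A reader might infer that 18 and 15 contradict each other. They do not, strictly: 18 is the number eligible, and 15 could be the number expected to take part. That step is unstated. With the SD held fixed, recruiting 18 per unit would raise power (0.83 with nine units if m = 15 lay behind 121), so planning on 15 is not imprudent in itself.

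A reader might also infer that the ninth unit is already used up and that the turnover statement is false. That holds only if the design effect used 15. With 18 or 20, the 18 units still give 0.80 or 0.82 after about 10% loss. The documents do not say which size was used, and they give no turnover rate against which to call the reserve insufficient. They therefore support neither printing one fixed power figure nor deleting the turnover statement outright.

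**Conclusion.** The point holds in a conditional form. It is certain that the unit count does not follow from the listed 18 staff per unit and that an unexplained 15 was used. If 121 came from the two-sided normal formula with the ANCOVA factor, 16 clusters of 15 give 0.74 to 0.79 on a cluster-level t test. That is below the stated 0.80 for each of the three unit sizes and whatever the missing SD. The 18 units enrolled give 0.79 to 0.84 with no loss and 0.77 to 0.82 at an assumed loss of about 10%. Part of the ninth unit per arm therefore makes up for the few clusters; at 15 per unit, all of it does.

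The size is modest. Even in the least favourable of these three cases, full enrolment gives 0.79 against a target of 0.80. The fault lies in the stated justification and the claimed reserve, not in a trial that is plainly too small.

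**What to change.** Restate the calculation for the 18 units, with no added enrolment:

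- Give the SD of the Emotional Exhaustion subscale and its source.
- Say how 18 eligible staff become 15 participants per unit, and use the participating number in both the design effect and the unit count.
- Use a between-cluster t reference (16 df for 18 units), and match it in the multilevel analysis with a small-sample method such as Satterthwaite or Kenward-Roger.
- Report power with no loss and at a stated loss rate.
- Keep the statement that the extra unit compensates for turnover, here and in the Discussion, only if the restated figure supports it.

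The cost is one rewritten paragraph and possibly a slightly lower stated power. The values in the table above depend on the assumed m and should not be copied in before the sponsor has confirmed the SD and the cluster size used.
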